## Abstract

**Background:**

The menstrual cycle and its impact on training and performance are of growing interest. However, evidence is lacking whether periodized exercise based on the menstrual cycle is beneficial. The primary purpose of this proposed randomized, controlled trial, the IMPACT study, is to evaluate the effect of exercise periodization during different phases of the menstrual cycle, i.e., comparing follicular phase-based and luteal phase-based training with regular training during the menstrual cycle on physical performance in well-trained women.

**Methods:**

Healthy, well-trained, eumenorrheic women between 18 and 35 years (*n* = 120) will be recruited and first assessed for physical performance during a run-in menstrual cycle at different cycle phases and then randomized to three different interventions: follicular phase-based training, luteal phase-based training, or regular training during three menstrual cycles. The training intervention will consist of high-intensity spinning classes followed by strength training. The menstrual cycle phases will be determined by serum hormone analysis throughout the intervention period. Assessment of aerobic performance (primary outcome) and muscle strength, body composition, and blood markers will be performed at baseline and at the end of the intervention.

**Discussion:**

With a robust methodology, this study has the potential to provide evidence of the differential effects of exercise periodization during different phases of the menstrual cycle in female athletes.

**Trial registration:**

ClinicalTrials.gov NCT05697263. Registered on 25 January 2023

## Administrative information

Note: This protocol is written with the support and guidance of the SPIRIT 2013 and the SPIRIT-outcomes 2022 items [1]. The numbers in curly brackets in this protocol refer to SPIRIT checklist item numbers (see http://www.equator-network.org/reporting-guidelines/spirit-2013-statement-defining-standard-protocol-items-for-clinical-trials/).

## Introduction

### Background and rationale {6a}

The menstrual cycle has the potential to affect sporting performance in female athletes. There is a growing interest of how exercise and performance can be optimized according to the menstrual cycle [2]. However, the effect of the hormonal variation on physical performance, as well as the impact of menstrual cycle-related symptoms, is only partly understood [3, 4].

Serum levels of the female sex hormones estradiol (E2) and progesterone (P4) vary greatly during the three phases of the menstrual cycle, i.e., the follicular phase (the first day of menstruation to ovulation), the ovulatory phase (at mid-cycle, 1–2 days), and the luteal phase (from ovulation to the next menstrual bleeding). E2 and P4 have receptors in most tissues of the human body and have important roles beyond the reproductive system [5]. Receptors for E2 (ERα and ERβ) have been detected in human skeletal muscle tissue [6, 7]. We have shown a substantial variation of receptor expression for ERs and for the progesterone receptor (PR) in the skeletal muscle throughout the menstrual cycle [8], which might influence neuromuscular performance and the effect of training during the menstrual cycle [8, 9].

It has been hypothesized that periodization of training in relation to the menstrual cycle can impact physical performance. Intensified strength training during the follicular phase has been proposed to improve muscle strength more than the same frequency of training during the luteal phase [10–13]. However, in a recent umbrella review with meta-analysis, the authors suggest that due to the methodological shortcomings in the reviewed articles, it would be highly premature to conclude that short-term fluctuations in ovarian hormones and their receptor levels in relevant target tissues noticeably influence acute exercise performance or longer-term adaptations to resistance training [3]. The authors call for evidence-based approaches for training recommendations for female athletes, based on research utilizing accurate and reliable menstrual cycle phase detection methods [3].

Menstrual cycle-related symptoms may affect physical exercise and performance. Menstrual-related pain, i.e., primary dysmenorrhea, is reported to affect most female athletes which often leads to absence from planned training [14, 15]. Furthermore, premenstrual symptoms (PMS) are experienced by most fertile-aged women and can be characterized by both physical symptoms (e.g., bloating, breast tenderness, headache) and psychological symptoms (e.g., depression, irritability, fatigue) occurring from the mid-luteal phase to the first days of menstrual bleeding [16, 17]. These symptoms have been reported to negatively influence athletic performance and well-being in female athletes [4, 14, 15].

### Objective {7}

The main objective of this planned trial, Impact of Menstrual cycle-based Periodized training on Aerobic performance: a Clinical Trial, "the IMPACT study", is to evaluate the effect of exercise periodization during different phases of the menstrual cycle, i.e., comparing follicular phase-based and luteal phase-based training with regular training throughout the menstrual cycle on physical performance in well-trained women.

Our primary hypothesis is that follicular phase-based training is superior to both luteal phase-based training and regular training throughout the menstrual cycle as it improves aerobic performance and muscle strength at higher extent.

The secondary hypothesis is that a variation in muscle morphology, e.g., gene expression, metabolic enzymes, markers of muscle protein synthesis, will be shown as a training effect, depending on the intervention group.

### Trial design {8}

The IMPACT study is a randomized, controlled trial, in which 120 exercising women will be allocated to three parallel groups, i.e., follicular phase-based training, luteal phase-based training, or regular training during three menstrual cycles. The IMPACT study will be preceded by a run-in cycle, see Fig. 1 for the study design. For reports, the trial will use the CONSORT 2010 explanation and elaboration: updated guidelines for reporting parallel group randomized trials [18] and the REPORT Trial guide for effective and transparent research reporting [19].

**Fig. 1 Fig1:**
[figure not shown]
Illustration of the study design with enrollment, assessments, and interventions. The early follicular phase (EFP) is set to cycle days (CD) 3–5, the late follicular phase (LFP) to CD 11–13, and the mid-luteal phase (MLP) to CD 20–22. The assessment of physical performance test at the LFP and MLP in the first menstrual cycle (run-in cycle) is not a part of the intervention

## Methods: participants, intervention, and outcomes

### Study setting {9}

The study will be carried out at research units at Karolinska Institutet (KI) and Karolinska University Hospital, Stockholm, Sweden. The training intervention will be carried out at specific healthcare centers in the Stockholm area. The recruitment is set to start in August 2023, and the study will run until the end of 2025.

### Eligibility criteria {10}

Healthy women with a regular aerobic training background will be assessed for eligibility in the study. The inclusion and exclusion criteria are listed in Table 1.

**Table 1 Tab1:** Criteria for eligibility

Inclusion criteria	Exclusion criteria
Females aged 18–35 years	Chronic disease
Regular menstruation (26–32 days interval)	Neurological disorder
Having a BMI within the interval of 19–26 kg/m^2^	Musculoskeletal injury in the last 6 months
Exercising ≤ three times/week the last 6 months	Irregular menstruation
Being able to fulfill the intervention period	Pregnancy or lactation in the last 6 months
	Use of hormonal contraceptives the last 3 months
	Use of regular medication for the last 3 months

*BMI* body mass index

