### Intervention

#### Explanation for the choice of comparators {6b}

In this randomized controlled trial, we have chosen to include well-trained females and will randomly assign them to the regimen of extended sessions of exercise during the follicular phase or during the luteal phase in the menstrual cycle and the control group of regular exercise throughout the menstrual cycle. All participants irrespective of intervention group or control will over the total intervention period obtain the same numbers of training sessions.

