**Fig. 2 Fig2:**
[figure not shown]
The disposing of spinning exercise and strength training in the two intervention groups (**A**, **B**) and the control group (**C**) in an average 28-day menstrual cycle

*Group A*: follicular phase-based training (spinning and strength training) five sessions per week during the follicular phase (approx. 14 days) and thereafter once a week during the luteal phase (approx. 14 days)*Group B*: luteal phase-based training (spinning and strength training) once a week during the follicular phase (approx. 14 days) and thereafter five sessions per week during the luteal phase (approx. 14 days) *Group C*: regular training (spinning and strength training) three times a week throughout the study period (control group)

In total, there will be 12 sessions of exercise per menstrual cycle during 3 consecutive cycles for all 3 groups.

At the end of the run-in cycle, randomization will be performed, and the participants will start the intervention immediately, at the following first day of menstruation. The intervention lasts for 3 menstrual cycles. The training program during the intervention consists of spinning exercise and muscular strength training, at the training centers in the Stockholm area, Sweden. The spinning exercises consist of 55 min of intermittent, high-intensity training (75–90 percent of maximal heart rate) with recovery periods in between. The heart rate during the spinning will be followed and registered on each occasion during the study period. Additionally, during at least 1 session per week, the total work in Joule will be monitored, utilizing a Wattbike during the exercise, and participants will be responsible for reporting these values in the REDCap® system. The strength training program consists of five exercises for the lower body (squats, lunges, hip thrust, and for core muscles back extension and isometric trunk, e.g., “plank”). The load and the number of repetitions of the strength training will be based on the participants’ fitness level and tested out during the run-in cycle. The range of repetition will be within 8–12 repetitions, and the number of sets will range within two to four sets.

During every training session, the participants will register their perceived exertion as well as the rating of perceived motivation prior to exercise in the REDCap®. To confirm the specific phase of the menstrual cycle, blood samples will be collected according to the EFP, LFP, and MLP (Fig. 1).

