The training intervention will not be supervised in a controlled environment; however, the women’s physical activity and training sessions will be followed continuously using the Oura smart ring. Moreover, during the intervention, the participant will in at least one training session per week monitor and report their achieved total work (J). Furthermore, they will self-score their motivation and perception in terms of their own effort and perceived exhaustion from every exercise session conducted. This will lead to an increased insight into the process behind trainability in female athletes in relation to the menstrual cycle.

The choice of outcome measures to evaluate physical performance was based on the demands of spinning exercises with aerobic intervals and muscular strengthening in the lower extremities. The primary outcome of TTE is widely used in a laboratory setting to measure aerobic performance and the average power output for TTE has shown to be higher compared to a TT protocol [33]. Self-paced TT is considered a more functional test with high ecological validity [33].

The proposed study may have some limitations. The results of the training intervention can only be generalized to female athletes with a moderate to high level of fitness and not to elite athletes. Due to the nature of the intervention, the participants cannot be blinded. Furthermore, the study coordinator will not be blinded to group allocation. However, the researcher analyzing the data will be blinded to the study intervention group.

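### The only training criterion in Table 1 is an upper limit of three sessions a week, which contradicts the well-trained population the trial says it studies

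*Protocol article*

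**What the plan says.** Eligibility criteria {10} opens with a general description: "Healthy women with a regular aerobic training background will be assessed for eligibility in the study". Table 1 then lists the criteria. One inclusion line concerns training: "Exercising ≤ three times/week the last 6 months". No other inclusion or exclusion criterion in the table refers to training frequency, training volume or fitness.

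The population is described in these other places:

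- Abstract, Methods: "Healthy, well-trained, eumenorrheic women between 18 and 35 years".
- Objective {7}: the comparison is with "regular training throughout the menstrual cycle on physical performance in well-trained women".
- Explanation for the choice of comparators {6b}, where it is presented as deliberate: "we have chosen to include well-trained females".
- Discussion, on limitations: the results "can only be generalized to female athletes with a moderate to high level of fitness and not to elite athletes".

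The Abstract's discussion and the Summary also direct the conclusions to female athletes.

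**The concern.** An eligibility criterion is operational text. It decides who is randomised, and readers use it to judge whom the result describes. A ceiling on training frequency cannot secure a well-trained sample. It removes the women who train most often and leaves the lower end open except for a general phrase with no threshold.

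The external validity of the trial is at stake. If recruitment follows the printed line, the conclusion for well-trained women and athletes would rest on a sample from which anyone training four or more times a week was barred. If recruitment follows a different rule, the published criterion misdescribes the sample and the trial cannot be replicated from it.

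**Working it through.** This is a comparison of texts. The article states no figure that needs reproducing.

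**Step 1. Apply the printed rule and its reverse to weekly frequency f.** The input is the Table 1 line.

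| f (sessions/week) | Printed rule, f ≤ 3 | Reversed rule, f ≥ 3 |
|---|---|---|
| 0, 1, 2 | meets the line | fails |
| 3 | meets the line | meets the line |
| 4, 5, 6, 7 | fails | meets the line |

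The two rules agree only at f = 3, so the direction of the sign determines eligibility for everyone else.

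**Step 2. Set the line beside the population statements.** Well-trained appears in the Abstract, in Objective {7} and in section {6b}. The Discussion speaks of athletes of moderate to high fitness. All of these describe a population with a floor on training, whereas Table 1 prints a ceiling. The lead-in to Table 1 points towards a floor but gives no frequency, duration or measure. The consent section {26a} ties consent to eligibility under the inclusion and exclusion criteria, which Table 1 lists.

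**Step 3. Look for a stated reason for a ceiling.** There is none. The Discussion's remark about elite athletes limits generalisation and is not linked to the criterion.

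**Step 4. Compare with the training delivered.** The inputs are the schedules in Intervention description {11a}, for a 28-day cycle of four weeks:

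- Group A: 5 × 2 + 1 × 2 = 12 sessions
- Group B: 1 × 2 + 5 × 2 = 12 sessions
- Group C: 3 × 4 = 12 sessions

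This matches the article's own total: "In total, there will be 12 sessions of exercise per menstrual cycle during 3 consecutive cycles for all 3 groups". The average is 12 / 4 = 3 sessions a week in every arm. For a woman who trained less than three times a week, each arm would therefore raise her session frequency. The sign thus also determines whether the trial studies women who increase their frequency or women who hold or reduce it.

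**Step 5. Sample size.** The 33 per group in Sample size {14} follows from the stated 0.70 SD, alpha 0.05 and 80% power. Eligibility does not enter that calculation, and no sample-size figure changes.

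**The case against.** The strongest reply is that the row should not be read alone. The sentence above the table limits assessment to women with a background of regular aerobic training, Trial design {8} describes the 120 participants as women who exercise, and the row itself begins by presupposing exercise. A reader might infer from the bare inequality that untrained or sedentary women are admitted. The text as a whole does not support that. It describes regular exercisers and leaves the minimum unquantified. This part of the reply stands. It does not address the other half of the contradiction, the exclusion of women who train four or more times a week.

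A second reply is that the ceiling may be deliberate. Every arm averages three sessions a week, and section {11d} bars other intense training, so a cap at three would spare women from cutting back. The Discussion also sets elite athletes aside. This is plausible, but the article does not say it. If it is the intention, the description well-trained and the missing minimum still need attention.

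A third reply is that the sign is a slip, either in typesetting or in the conversion of the text. A typographical slip is quite possible. Nothing in the text indicates a conversion fault, although one cannot be fully excluded, and a look at the source settles it.

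**Conclusion.** The contradiction holds. The only training criterion in Table 1 is an upper limit of three sessions a week with no quantified minimum, and it conflicts with the population named in the Abstract, the Objective, the choice of comparators and the Discussion. This rests on the printed sign being the one in the source. It describes the criterion as written. The article does not show who was actually enrolled.

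Three stronger conclusions are not supported:

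- **That the sign is certainly reversed.** This is a likely explanation, but a deliberate ceiling with a loosely worded population cannot be excluded.
- **That the criterion costs power.** A reader might infer that mixing training levels inflates the variance of time to exhaustion (TTE). The article gives no raw SD, no SD of change and no effect by training level. The direction is also uncertain, because a minimum with no upper limit could admit just as wide a spread.
- **That the comparison between arms is invalid.** Randomisation protects it under either reading.

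The damage is to the definition of the sample and to the claim about whom the result applies to. Because this is a live eligibility rule that conflicts with the stated objective, it should be corrected before the results are reported.

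**What to change.** Reconcile Table 1 with the stated population, in one of two ways:

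1. If the sign is reversed, correct the line to a minimum.
2. If the ceiling is intended, state a minimum training level, give the reason for the ceiling, and change the references to well-trained women and athletes in the objective, discussion and conclusions so that they describe the women admitted.

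In either case, check the women already enrolled against the corrected criterion and report how many fall outside it. Recruitment began in August 2023 and the protocol version is dated 5 January 2024, so some women are likely to have been enrolled under the printed line. Section {26b} already provides for a review of training habits and the International Physical Activity Questionnaire at enrolment, so no new data are needed.

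The cost is one corrected line, or a few if the second route is taken, an amendment notice through the channels in section {25}, and a check of data already held.

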### Who will take informed consent? {26a}

Potential participants will be given oral and written information about the aims of the study and its procedure. If eligible according to the inclusion and exclusion criteria, they will be asked to give their written consent to participate. The project coordinator will take the informed consent and scan it into the data storing system: Research Electronic Data Capture (REDCap®)

### Additional consent provision for collection and use of participant data and biological specimens {26b}

On the consent form, it is stated in a separate paragraph that participants give consent to the collection of blood plasma and biopsy specimens to be stored in a research biobank. The biobank is under the legal supervision of the Swedish Data Protection Regulation. The consent to collection of biopsy specimens will be given of a subgroup of participants.

Upon enrollment, a comprehensive anamnesis of each participant will be performed. This aims to review gynecological history, general health, medication, historical and recent training habits, sleeping, and nutritional status. Physical training patterns in the past and present will be evaluated using the International Physical Activity Questionnaire (IPAQ) [20].

#### Run-in cycle

The study starts with a run-in cycle including assessments at the early follicular phase used as a baseline for the IMPACT study (Fig. 1). The purpose of the run-in cycle is to compare physical performance in different phases of the menstrual cycle without periodization and to assess women’s individual cycle.

During the run-in cycle, the participants will be assessed for the outcome’s measures at three phases during the first menstrual cycle (Fig. 1):

*Early follicular phase (EFP)*, cycle days (CD) 3–5 (low levels of E2 and P-4)* Late follicular phase (LFP)*, CD 11–13 (high levels of E2)*Mid luteal phase (MLP)*, CD 20–22 (high levels of E2 and P-4)

Cycle day for examination will be adapted to the participant’s cycle length. The first visit during the run-in cycle is the baseline in the IMPACT study.

Prior to the test protocol, a 10-min warming up on a cycle ergometer will be performed. The test protocol includes several tests of physical performance (see the “Outcomes” section) which will take approximately 75 min/participant, with standardized rest between every test. Nutritional recommendations will be provided to the participants to standardize the diet 24 h prior to the day of testing. In addition, participants will be required to keep an unchanged diet throughout the study period.

#### Run-in cycle 1st visit/baseline

A fasting blood sample of 25 ml and a urine sample will be collected in the morning between 08:00 and 10:00 AM before breakfast and after refraining from alcohol, caffeine consumption, and any intense physical activity or sports practice 24 h prior to the testing day for analysis of hormones and binding proteins.A light breakfast will be served.Physical performance tests including aerobic performance and aerobic capacity, peak power output, isokinetic muscle strength, and jumping performance will be performed.Body composition will be measured by dual-energy X-ray absorptiometry (DXA).Subjective rating of menstrual cycle-related symptoms, e.g., dysmenorrhea and PMS, will be performed every day from baseline and during the entire study period.Registration of daily physical activity, sleeping pattern, heart rate, and heart rate variability will be monitored by the Oura smart ring (Oura Health Ltd., Oulu, Finland).Muscle biopsy will be obtained under local anesthesia from the m. vastus lateralis in a subgroup of participants (*n* = 45). The muscle biopsies will be collected at EFP, the day after the physical assessments.

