#### Run-in cycle 2nd visit

*•* A non-fasting blood sample of 10 ml will be collected for the determination of the cycle phase.

*•* Physical performance tests include aerobic performance, aerobic capacity, peak power output, isokinetic muscle strength, and jumping performance.

*•* For the detection of ovulation, the participants will use urinary sticks (Ovustix, Clearplan, Unipath Limited, Bedford, UK) measuring the luteinizing hormone (LH) surge.

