#### Provisions for post-trial care {30}

There is no anticipated harm and compensation for trial participation. This study focuses on health and wellness, and all participants will be given the same amount of training throughout the trial. There is no provision for post-trial care.

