##### Muscle biopsy

In a subset of participants (*n* = 45), resting muscle biopsy specimens are obtained at baseline and at follow-up under local anesthesia from the distal portion of the m. vastus lateralis of the quadriceps femoris muscle of one leg using a Weil-Blakesley conchotome (AB Wisex, Mölndal, Sweden) under standardized medical supervision. In the specimen, analyses of fiber composition, relative fiber area, and number of capillaries for each fiber group are performed. The concentration of hormone receptors, metabolic enzymes, markers of muscle protein synthesis, and markers of atrophy will be determined.

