#### Plans for collection, laboratory evaluation, and storage of biological specimens for genetic or molecular analysis in this trial/future use {33}

Blood will be drawn from the trial participants on 13 occasions, with a total volume of 160 ml. At baseline assessment (week 1) and at follow-up (week 17), 25 ml blood will be drawn, and at the remaining 11 occasions, an amount of 10 ml blood will be drawn on each occasion (Fig. 1).

Muscle biopsies from the m. vastus medialis will be collected at baseline and follow-up (before and after intervention) in a sub-sample of participants. At each collection, two samples will be taken.

Blood samples and muscle tissue will be stored in the research biobank at − 80 °C until the trial is completed, and all planned analyses are performed. Any additional studies on the collected biological material will need new approval by the Committee of Ethics and approval according to the Swedish Data Protection Regulation and the Swedish Data Protection Law. Trial participants can without any consequences decline to donate blood and muscle tissue for the biobank for future unspecified research. Participants can at any time request to have their biological material destroyed, with such request, the biological material will immediately undergo destruction.

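### In the 45 biopsied women, the run-in comparison of cycle phases is fully confounded with before versus after a quadriceps biopsy, and the stated model does not separate the two

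*Protocol article*

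**What the plan says.** All places are in the protocol article.

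- **Timing of the first biopsy** (Run-in cycle 1st visit/baseline): the vastus lateralis is biopsied in a subgroup of 45 women. "The muscle biopsies will be collected at EFP, the day after the physical assessments".
- **The procedure** (Muscle biopsy; item 33 on biological specimens): tissue is taken under local anaesthetic with medical supervision, "from the distal portion of the m. vastus lateralis of the quadriceps femoris muscle of one leg". Item 33 adds "At each collection, two samples will be taken", but names the vastus medialis as the muscle.
- **Test windows** (Fig. 1 legend): "The early follicular phase (EFP) is set to cycle days (CD) 3–5, the late follicular phase (LFP) to CD 11–13". Days 20–22 are the window for the mid-luteal (MLP) tests. The Run-in cycle section adds "Cycle day for examination will be adapted to the participant’s cycle length".
- **What is repeated after the biopsy** (Run-in cycle 2nd visit): "Physical performance tests include aerobic performance, aerobic capacity, peak power output, isokinetic muscle strength, and jumping performance". The 3rd visit lists the same tests and adds muscle endurance.
- **Purpose and analysis**: the Run-in cycle section gives comparison of performance between phases as a purpose of the run-in. Item 20a analyses that comparison with linear mixed models over EFP, LFP and MLP and mentions no allowance for the biopsy.
- **Harm** (Provisions for post-trial care {30}): "There is no anticipated harm and compensation for trial participation".

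**The concern.** The phase comparison is made within women, so each woman is her own control. That works only if nothing other than cycle phase changes systematically between visits. In the biopsied women something does: two samples are cut from a muscle that cycling, knee extension and jumping all load, always after the EFP tests and always before the LFP and MLP tests. Any residual soreness or guarding would lower the later results in those women only, and the model would count it as a phase effect. It could also hide a real improvement at LFP.

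Randomisation gives no protection, because it takes place at the third run-in visit and the comparison is within women rather than between arms. At stake is the run-in result, which is a stated aim of the study but not its primary outcome.

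There is also a consistency problem in the text. The no-harm statement is supported by reference to the focus on health and the equal amount of training, and does not consider an invasive procedure done at baseline and again at follow-up.

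**Working it through.** The plan gives no figure for a biopsy effect, so there is none to reproduce. The check is day arithmetic followed by a range of assumed effects.

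**1. Gap between biopsy and later tests (28-day cycle).** Inputs: EFP days 3–5, LFP days 11–13, MLP days 20–22, biopsy one day after the EFP tests.

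- Biopsy day = (3 to 5) + 1 = day 4 to 6.
- Gap to LFP: shortest 11 − 6 = 5 days, longest 13 − 4 = 9 days.
- Gap to MLP: shortest 20 − 6 = 14 days, longest 22 − 4 = 18 days.
- Gap to the start of the intervention (day 1 of the next cycle, i.e. day 29): 29 − 6 = 23 to 29 − 4 = 25 days.

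Test days move with cycle length, and cycles of 26–32 days are eligible. If only the follicular part varies (an assumption), the gap to LFP is 3–7 days at 26 days and 9–13 days at 32 days.

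**2. Confounding.** The order is the same in every biopsied woman:

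| Visit | With biopsy (45) | Without biopsy (120 − 45 = 75) |
|---|---|---|
| EFP | before | no biopsy |
| LFP | after, 5–9 days | no biopsy |
| MLP | after, 14–18 days | no biopsy |

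Within the 45, the EFP–LFP and EFP–MLP contrasts cannot be told apart from before versus after biopsy. The 75 others make separation possible, but only if the model uses biopsy status.

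**3. Size.** Share biopsied = 45/120 = 0.375. If the biopsy lowers LFP performance by d SD in biopsied women, the whole-sample contrast shifts by 0.375 × d. The documents give no value for d, so 0 to 0.5 is assumed. For scale, the standard error (SE) of a paired contrast in 120 women, with equal variances and within-woman correlation r, is √(2(1 − r)/120). This gives 0.058 SD at r = 0.8 and 0.041 SD at r = 0.9. Both values of r are assumptions.

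| d (SD, assumed) | Shift 0.375 × d (SD) | Shift in SEs, r = 0.8 | Shift in SEs, r = 0.9 |
|---|---|---|---|
| 0 | 0 | 0 | 0 |
| 0.1 | 0.04 | 0.6 | 0.9 |
| 0.2 | 0.08 | 1.3 | 1.8 |
| 0.3 | 0.11 | 1.9 | 2.8 |
| 0.5 | 0.19 | 3.2 | 4.6 |

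So an effect that is small in each biopsied woman could matter for this contrast, and an effect near zero would not.

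**4. Price of separating the two.** With a biopsy-by-visit term, the biopsy-free phase contrast is estimated essentially from the 75 women without biopsy, as it is in an analysis restricted to them. Its SE rises by about √(120/75) = √1.6 = 1.26 under either option.

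**The case against.** The strongest reply is that this is a condensed article. One sentence covers the run-in analysis, and covariates or sensitivity analyses may sit in a statistical analysis plan that is not shown. That has force: the absence of a biopsy term here does not prove that none is planned. But the confounding does not rest on silence. It follows from the stated visit order, and the article names both the comparison and the model.

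The second reply is that nothing in the documents shows any deficit 5–9 days after a biopsy, that only one leg is biopsied, and that cycling and jumping use both. This stands. The effect could be zero, and it need not be equal across outcomes.

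Three stronger readings are tempting and should not be adopted:

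- **That biopsy effects go unmonitored.** The Muscle biopsy section requires medical supervision. Item 22 collects every kind of adverse event during the trial and provides for referral. Item 11b applies stopping rules if signs of illness appear during testing. Daily ratings and further visits follow the first biopsy.
- **That half of the biopsy sessions have no later study contact.** The day-after rule is written only under the baseline visit; for the second biopsy the text says only that it is taken at follow-up. Item 30 does say "There is no provision for post-trial care", but no section says that contact or adverse event collection ends before or at that biopsy.
- **That the primary result is biased.** Baseline tests precede the first biopsy, and the intervention starts about 23–25 days after it. The documents show no direct route from the biopsy to the randomised comparison of time to exhaustion.

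**Conclusion.** The point holds as a limited one about the run-in analysis. In 45 of 120 women (37.5%), phase is fully confounded with before/after biopsy, and the stated model does not separate them. The 5–9 day gap assumes a 28-day cycle and tests within the stated windows. The possible shift of 0–0.19 SD in the EFP–LFP contrast is an assumed effect of 0–0.5 SD multiplied by 0.375. It shows what could happen and is not an estimate of what will.

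This is a minor but worthwhile correction, because data already being collected can settle it. Two textual inconsistencies stand independently of the arithmetic: the blanket no-harm statement set against a supervised biopsy under local anaesthetic, and vastus lateralis in two sections against vastus medialis in item 33.

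**What to change.** 1. In the run-in phase model, add biopsy status and its interaction with visit, and report the phase contrast for women without biopsy. Alternatively, keep the planned model and also report the phase comparison in the 75 women without biopsy as a sensitivity analysis. State the choice before the run-in data are analysed. The interaction estimate reads as a biopsy effect only if phase effects are otherwise alike in the two subgroups; the article does not say how the 45 are chosen.
2. Reconcile the no-harm statement in item 30 with the biopsy described under Muscle biopsy.
3. Reconcile the name of the biopsied muscle between the baseline visit, Muscle biopsy and item 33.

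The cost is one model term or one repeat analysis, two text corrections, and an SE about 1.26 times larger for the biopsy-free contrast under either option. No extra visit, measurement or participant is needed.
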